**Methods and analysis:**

We present the Multidisciplinary lifestyle Interventions for Neurological Disorders during the Silent phase (MINDS) protocol, a randomized controlled trial of MLI in neurologically healthy older adults (≥ 50 years old) exhibiting elevated risk for common neurological disorders: stroke, epilepsy, Parkinson’s Disease, or Alzheimer’s disease and related dementias. Participants will be randomly assigned to intervention (*n* = 100) or control (*n* = 100) groups. The intervention group will receive 3 months of weekly 2-hour sessions on diet education, yoga, music therapy, and cognitive skills training. The participants’ neurological health and engagement in relevant lifestyle practices will be assessed at regular intervals for 12 months. Neuroimaging and samples for multi-omic analyses will be collected at baseline, and at 3 months and 12 months after enrollment. Primary outcomes will be signs of progression of the neurological disorder risk that qualified them for study enrollment or a clinical diagnosis of the disorder. Secondary and exploratory outcomes will be based on self-reported health and multi-omic data. Data analysis will include between-group and longitudinal within-group analyses.

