## Methods

### Aims of the trial

We aim to test the impact of MLI on neurological disorder progression in patients identified as at risk of stroke, epilepsy, PD, or ADRD associated with the a) transition from ‘at-risk’ preclinical (silent) stage to the worsening of clinicopathological changes or a diagnosis of a neurological disorder and b) the progression of pathological changes leading to the development of a neurological disorder. An additional goal of the MINDS study is to identify biomarkers that predict MLI’s efficacy in disease prevention or neuropathology progression in these patients.

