### Study description and study design

This 12-month study is an open-label randomized controlled trial with parallel participant assignment into intervention and control arms (Fig. 1). The study will enroll individuals from the ongoing Cleveland Clinic Brain Study (CCBS), a longitudinal study of neurologically healthy adults (≥ 50 years old) at the Cleveland Clinic academic medical center, who are at-risk for transitioning to a neurological disorder [12]. A study team member who has been trained in the study protocol will provide the participant with information related to the study, obtain informed consent, and enroll the participant in the study if they choose to participate. CCBS participants undergo a thorough history and physical examination conducted by advanced practice providers with specialization in neurological care; a battery of surveys on quality of life, sleep, and mental health; neuropsychological testing [NP; includes the Brief Assessment of Cognitive Health (BACH), Tombaugh Trails test, Rey Auditory Verbal Learning Test (RAVLT), Boston Naming Test (BNT), Digit Span, Judgment of Line Orientation (JLO), and the Activities of Daily Living Questionnaire (ADLQ)]; brain magnetic resonance imaging (MRI); optical coherence tomography (OCT); and overnight electroencephalography (EEG) and polysomnography (PSG) along with biospecimen (blood, stool) collection for genomics, proteomics, and metabolomics analyses. Questionnaires include Perceived Stress Scale (PSS-10); Generalized Anxiety Disorder 7 Item (GAD-7); Patient Health Questionnaire Depression Scale (PHQ-8); Neuro-QoL (Quality of Life in Neurological Disorders) surveys for Sleep Disturbance, Ability to Participate in Social Roles and Activities, Lower Extremity Function, and Upper Extremity Function; PROMIS (Patient-Reported Outcomes Measurement Information System) Global Health, Healthy Aging Activity Engagement Scale, and General Self Efficacy Scale.This 12-month study is an open-label randomized controlled trial with parallel participant assignment into intervention and control arms (Fig. 1). The study will enroll individuals from the ongoing Cleveland Clinic Brain Study (CCBS), a longitudinal study of neurologically healthy adults (≥ 50 years old) at the Cleveland Clinic academic medical center, who are at-risk for transitioning to a neurological disorder [12]. A member of the study team who has been trained in the study protocol will provide the participant with information related to the study, obtain informed consent, and enroll the participant in the study if they choose to participate. CCBS participants undergo a thorough history and physical examination conducted by advanced practice providers with specialization in neurological care; a battery of surveys on quality of life, sleep, and mental health; neuropsychological testing [NP; includes the Brief Assessment of Cognitive Health (BACH), Tombaugh Trails test, Rey Auditory Verbal Learning Test (RAVLT), Boston Naming Test (BNT), Digit Span, Judgment of Line Orientation (JLO), and the Activities of Daily Living Questionnaire (ADLQ)]; brain magnetic resonance imaging (MRI); optical coherence tomography (OCT); and overnight electroencephalography (EEG) and polysomnography (PSG) along with biospecimen (blood, stool) collection for genomics, proteomics, and metabolomics analyses. Questionnaires include Perceived Stress Scale (PSS-10); Generalized Anxiety Disorder 7 Item (GAD-7); Patient Health Questionnaire Depression Scale (PHQ-8); Neuro-QoL (Quality of Life in Neurological Disorders) surveys for Sleep Disturbance, Ability to Participate in Social Roles and Activities, Lower Extremity Function, and Upper Extremity Function; PROMIS (Patient-Reported Outcomes Measurement Information System) Global Health, Healthy Aging Activity Engagement Scale, and General Self Efficacy Scale.

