#### Cognitive skills

This intervention teaches participants cognitive compensatory strategies and more general psychosocial strategies to optimize brain health. Brain health strategies include mental engagement, social engagement, exercise, and stress management. Cognitive compensatory strategies are intended to mediate and accommodate for any cognitive difficulties (such as impaired working memory). These strategies may increase functional independence, reduce the impact of cognitive changes related to aging, and delay the onset and progression of neurological disorders [16, 17]. Sessions include group counseling led by a licensed neuropsychologist.

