### Outcome measures

The primary outcome of the MINDS study is the progression in the clinicopathological features specific to the neurological disorder for which the participant has a risk factor. Progression criteria for each disorder are described in Table 2. The secondary outcomes include the appearance of inclusion criteria (see Table 2) for neurological disorders other than the one that led to their study enrollment and self-report questionnaires in the following domains: quality of life in neurological disorders, depression symptoms, anxiety symptoms, self-efficacy, stress, and global health (see Table 3 for details). Exploratory outcomes for this study are neurological disease-related genomic, proteomic, metabolomic, and gut microbiome RNA biomarkers collected at 3 time points. The schedule for all outcome measurements and other assessments is reported in Table 1. Multi-omics data to be explored in the study includes the following:

**Table 2 Tab2:** Inclusion and progression criteria by neurological disorder. Inclusion and progression criteria for each neurological disorder described

Neurological Disorder	Inclusion Criteria	Progression Criteria
Stroke	Moderate to severe white matter changes on MRI	Additional asymptomatic cortical infarct **Or** Further increase in white matter disease MRI changes **Or** Clinical stroke
Epilepsy	At least one epileptiform discharge (spike, polyspike, sharp wave) on overnight EEG	Increase in burden (per hour) of epileptiform discharges **Or** Electrographic seizure on EEG **Or** Clinical seizure
ADRDs	≤ 40 on subjective memory self-assessment on BACH **And** At least one memory task score (RAVLT Trial 7 or Total Score) to ≤ 1.5 SD below population mean	Increase in number of NP testing domain scores to ≤ 1.5 SD below population mean **Or** Drop in NP testing scores to ≤ 2SD below the mean **Or** Clinical diagnosis of dementia
Movement Disorders	Hyposmia (age and sex matched score ≤ 10th percentile) on the University of Pennsylvania Smell Identification Test (UPSIT)	> 4 points increase on modified MDS-UPDRS administered remotely **Or** Parkinson’s Disorder diagnosis **Or** Initiation of dopaminergic therapy

**Table 3 Tab3:** Self-report questionnaires. Self-report questionnaires and phenotypic domains

Domain	Questionnaire Name
Stress	Perceived Stress Scale (PSS-10)
Generalized anxiety symptoms	Generalized Anxiety Disorder 7 Item (GAD-7)
Depression symptoms	Patient Health Questionnaire Depression Scale (PHQ-8)

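### In the ADRD stratum, two of the three primary progression criteria are test scores for abilities that only the intervention arm is taught to compensate for, so fewer progressions may partly reflect strategy use.

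*Protocol article*

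**What the plan says.** The primary outcome is "progression in the clinicopathological features specific to the neurological disorder for which the participant has a risk factor" (Outcome measures). For ADRD, Table 2 gives three criteria joined by 'or':

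- "Increase in number of NP testing domain scores to ≤ 1.5 SD below population mean"
- "Drop in NP testing scores to ≤ 2SD below the mean"
- "Clinical diagnosis of dementia"

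The NP battery includes "Rey Auditory Verbal Learning Test (RAVLT), Boston Naming Test (BNT), Digit Span" (Study description and study design). Table 1 repeats NP testing at months 3 and 12.

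The intervention arm receives "weekly 2-hour sessions on diet education, yoga, music therapy, and cognitive skills training" (abstract). The section Cognitive skills says that "Cognitive compensatory strategies are intended to mediate and accommodate for any cognitive difficulties (such as impaired working memory" is the example given. Controls receive standard of care and the trial is open-label. The stated aims include the effect of the intervention on "the progression of pathological changes leading to the development of a neurological disorder" (Aims of the trial).

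**The concern.** Someone who learns to organise or chunk material may score higher on list learning or digit span while the underlying disease is unchanged. One arm is taught such strategies and the other is not. In the ADRD stratum, scores on tests of these abilities then decide whether a participant has progressed.

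The section Cognitive skills itself lists a smaller impact of cognitive changes separately from a delay in onset and progression. Table 2 cannot tell the two apart. Blinding the experts who check and analyse the data (Arms and interventions) does not help, because the scores themselves would move. The sensitivity analyses in the Data analysis plan are directed at confounders such as baseline imbalance and non-compliance, and do not address this.

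At stake is what a favourable ADRD result may be said to show: slower disease, or better performance on tests.

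**Working it through.** **The plan's own figure.** This point does not dispute it. Cohen's d = 0.8 converts to OR = exp(0.8π/√3) = 4.27. With 200 × 0.9 = 180 analysed (90 per arm) and 18% progression in controls, the intervention odds are (0.18/0.82)/4.27 = 0.0514, a rate of 4.9%. Normal-approximation power is 0.794, in line with the stated 0.8. The 4.27 refers to the whole trial, not to one stratum.

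**Effect within the ADRD stratum.** The documents give no strategy effect, no score distribution and no number of NP domains. All of the following are assumptions:

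- 3 or 5 domain scores, true mean −0.5 SD, between-person SD 0.85, inter-domain correlation 0.3, retest error SD 0.5.
- Entry requires one domain at or below −1.5 SD at baseline, standing in for the RAVLT criterion.
- An event is a rise in the number of domains at or below −1.5 SD, or any score newly at or below −2 SD (one reading of the second criterion).
- There is no disease change in either arm. A gain is added to two domains at follow-up, in the intervention arm only.

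| Gain on two domains | 5 domains: rate (OR) | 3 domains: rate (OR) |
|---|---|---|
| 0 (control) | 35.9% | 25.8% |
| 0.2 SD | 29.6% (1.33) | 18.7% (1.51) |
| 0.3 SD | 27.0% (1.51) | 16.0% (1.83) |
| 0.5 SD | 22.9% (1.88) | 11.7% (2.63) |

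The OR is control odds over intervention odds. For example, with 5 domains at 0.2 SD: (0.359/0.641)/(0.296/0.704) = 1.33.

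**Effect on the pooled test.** A simpler model serves here: one normal score per ADRD participant, 18% control progression in every stratum, and 90 per arm. A gain δ lowers the ADRD rate to Φ(Φ⁻¹(0.18) − δ) = Φ(−0.915 − δ):

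- δ = 0.2: 13.2% (OR 1.44)
- δ = 0.3: 11.2% (OR 1.74)
- δ = 0.5: 7.8% (OR 2.58)

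These ORs lie in the same range as the simulation. With ADRD share s, the intervention arm's overall rate is s × (ADRD rate) + (1 − s) × 18%. The chance that a two-sided Fisher test reaches p ≤ 0.05, by exact enumeration, is:

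| ADRD share | δ = 0.2 | δ = 0.3 | δ = 0.5 |
|---|---|---|---|
| 25% | 3.6% | 4.0% | 5.0% |
| 50% | 4.7% | 6.5% | 11.3% |

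With no shift it is 3.2%. In the limiting case where every participant is in the ADRD stratum, it would be 10.2%, 19.4% and 45.9%.

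**The case against.** The case against has several parts.

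**Content and dose.** The protocol describes compensatory and psychosocial strategies with group counselling. It does not describe rehearsal of test items, and working memory is its only named example. Two of four domains per week for 12 weeks gives 12 × 2/4 = 6 sessions of 50 minutes, about five hours. Month-12 testing comes nine months after the sessions end. All of this stands. It argues for a modest gain, but not for none. A reader might infer that participants are coached on the tests themselves. The article does not say so, and Supplemental Material 2, which describes the sessions, is not at hand.

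**Scope.** The overlap does not extend to naming or line orientation, to the dementia diagnosis, or to the criteria of the other three strata, none of which uses NP scores. This stands too, and is why the gain is limited to two domains above.

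**Tempting stronger readings.** A reader might infer that strategy use alone could produce an odds ratio above the 4.27 used for power. That happens only with a 0.5 SD gain on every domain and no entry criterion (about 4.7 to 5.6), and it sets a stratum figure against a whole-trial one. A reader might also infer that the ADRD stratum could by itself produce a positive primary result. At a 25% share the false-positive rate does not pass the nominal 5%, and the actual share is not given.

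**Article format.** Analysis detail may sit in an analysis plan that is not shown. But the mismatch is between the outcome definition and the intervention content, and both are stated here.

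**Biomarkers.** Exploratory outcomes are already to be compared between arms. That is true, but nothing ties them to the reading of the ADRD result.

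**Conclusion.** The concern holds as a limit on interpretation, confined to the ADRD stratum. Two of its three progression criteria cannot separate strategy use from slower disease, and nothing in the text does so by other means. Under assumed gains of 0.2 to 0.5 SD on two domains, with the entry criterion applied, the spurious odds ratio within the stratum is about 1.3 to 2.6. In the pooled test the effect is slight if ADRD is a quarter of the sample (about 4–5% false positives) and material if it is half (about 5–11%), against 3.2% with no shift. The gain, the score model and the ADRD share are all assumptions. The sample-size statement is unaffected. The change is worth making, because without it a favourable ADRD result would be read as slowed disease progression.

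**What to change.** Keep the primary outcome and its test, and pre-specify the following:

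1. A companion analysis in which the ADRD stratum counts only a clinical diagnosis of dementia and the other three strata are unchanged, reported beside the primary result.
2. Progression rates by arm within each of the four strata.
3. A sentence stating that a difference driven by the ADRD NP-score criteria will be described as better cognitive test performance and not as slowed disease progression.
4. A between-arm comparison of Aβ42/Aβ40, pTau 181 and neurofilament light in the ADRD stratum, labelled supportive only. The section Proteomics already lists these assays.

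The cost is one extra analysis, one table and a sentence, with no new data. The downside is that few dementia diagnoses are likely in 12 months among people enrolled as neurologically healthy. The companion analysis will have wide intervals, and the other three strata will largely decide its direction. It should inform interpretation and not serve as a strict condition for a positive conclusion.

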#### Whole genome sequencing

will be used to score possible pathogenic variants for any neurological disorders based on ClinVar annotation and will extract the necessary genotypes to calculate polygenic risk scores (PRS) for each participant using publicly available Genome-Wide Association data for Parkinson’s Disease, Alzheimer’s Disease, Epilepsy, and Stroke.

#### Proteomics

Proteomic analyses will use O-Link NeurX 96 to analyze 92 exploratory and established protein markers of neurology-related diseases and biological processes. Neurofilament light polypeptide will be measured using the R-PLEX Human Neurofilament L Assay from Meso Scale Discovery (K1517XR, MSD; Rockville, MD). Protein assays for Aβ40, Aβ42, total tau, and pTau 181 will be performed using commercially available digital immunoassays (Neurology 3-Plex A Advantage Kit and pTau-181 Advantage V2.1 Assay Kit) on the Simoa SR-X platform (101,995 and 104,111, Quanterix; Billerica, MA) according to the manufacturer’s instructions.

#### Metabolomics

Sample metabolomes will be analyzed using an untargeted metabolomics approach involving metabolite extraction prior to analysis by high-performance liquid chromatography coupled to mass spectrometry (LC-MS). Resulting LC-MS data will be analyzed to determine the relative abundance of the observed metabolites across all samples and to identify metabolites.

#### Gut microbiome

We will use whole genome sequencing to analyze the gut microbiome’s taxonomic and functional dynamics by examining the microbial community’s complete (meta)transcriptome within the gut using MetaPhlAn4 and HUMAnN 3.

#### Sample size calculation

Our enrollment goal is 200 participants randomized to each group (intervention and control). Based on an attrition rate of 10%, we estimate we will have 180 participants with data for analysis. For primary outcomes analysis of binary outcomes (i.e., progression/no progression), the detection of a standard large effect size (odds ratio = 4.27, converted from Cohen’s *d* = 0.8) of the intervention at 0.8 power with a two-sided alpha of 0.05 would require 18% of the control group attaining progression. For secondary outcomes between group mixed-effects regression analysis, we will be able to detect a medium effect size (Cohen’s *f* = 0.27) at 0.8 power and a 5% significance level.

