### Arms and interventions

Two hundred participants will be randomized equally to two study arms (*n* = 100 each): the intervention arm and the control observational arm. The sequence of group allocation was generated by the study data scientist using computer-generated random numbers and uploaded to the secure study REDCap database, where it can be administered by the study team. Each participant’s start date is based on participant availability, and, once enough participants (at least five) are identified that can meet at the same time, an intervention group and matching control group of comparable size will begin study activities on the same schedule. The experts completing quality assurance of the testing and analysis of the multi-omic data, including imaging, electrophysiology, and patient reported outcome measures are blinded to group allocation.

The intervention group will receive synchronous, virtual 2-hour weekly intervention sessions for 12 weeks. The control group will receive the standard of care during this time. Both groups will receive a MINDS study activity survey (see Supplemental Material 1) every 2 weeks during the first 12 weeks, followed by every month until the end of the 12-month study period. Each two-hour intervention session includes check-in and discussion of homework, followed by two 50-minute sessions, split evenly between two of the four intervention domains, with rotation through the domains and topics each week so that participants receive an even dose of intervention domain. See Supplemental Material 2 for an overview of the 12-week intervention sessions.

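### The sample-size section sets enrolment at 200 per group, while the rest of the article, and that section's own attrition and power figures, describe 200 in total

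*Protocol article*

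**What the plan says.** The protocol article gives the trial's size in three places.

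- Abstract, Methods and analysis: "Participants will be randomly assigned to intervention (*n* = 100) or control (*n* = 100) groups".
- Arms and interventions: "Two hundred participants will be randomized equally to two study arms (*n* = 100 each").
- Sample size calculation: "Our enrollment goal is 200 participants randomized to each group (intervention and control").

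The sample-size section then continues: "Based on an attrition rate of 10%, we estimate we will have 180 participants with data for analysis". For the binary primary outcome it assumes a large effect ("odds ratio = 4.27, converted from Cohen’s *d* = 0.8") and says that detecting it "at 0.8 power with a two-sided alpha of 0.05" requires 18% progression in the control group. The Perspective section repeats the 18% condition as a limitation of the study.

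**The concern.** The first two statements give 200 participants in total. The third, as written, gives 400. They cannot all be right, and the odd one out stands in the section a reader consults for the enrolment target.

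The wording could be harmless if 180 were meant per group, since 200 per group less 10% is also 180. The sample-size paragraph would then be consistent with itself, and the conflict would lie only with the abstract and the arms section. So it has to be settled which design the power statement belongs to.

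What is at stake is how the completed trial is read. If recruitment closes at 100 per arm, one section says the target was met and another says the trial stopped at half of it. The Perspective section already concedes that the required progression rate may be hard to reach in 12 months, so a null primary result is foreseeable. Its interpretation depends partly on whether the trial was fully enrolled.

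**Working it through.** **Inputs.** Enrolment of 200 per group or 200 in total, 10% attrition, 180 analysable, d = 0.8, odds ratio 4.27, 18% control progression, power 0.80 and two-sided alpha 0.05 (Sample size calculation; totals also from the abstract and Arms and interventions). Fisher's exact test as the primary test (Data analysis plan).

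**Step 1: attrition.** Analysable N = enrolled × (1 − 0.10).

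- 200 in total: 200 × 0.9 = 180, or 90 per arm. This is the stated figure.
- 200 per group: 400 × 0.9 = 360, or 180 per arm.

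**Step 2: effect size.** OR = exp(d·π/√3) = exp(0.8 × π/√3) = 4.268, which agrees with the stated 4.27.

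**Step 3: intervention-arm rate.** Control odds are 0.18/0.82 = 0.2195. Dividing by 4.27 gives 0.0514, and 0.0514/1.0514 = 0.0489. The comparison is 18% against 4.89%.

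**Step 4: power by arm size.** With n per arm and p̄ = (0.18 + 0.0489)/2 = 0.1144, the normal approximation is

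power = Φ{ [ |p₁ − p₂|·√n − 1.96·√(2p̄(1 − p̄)) ] / √(p₁(1 − p₁) + p₂(1 − p₂)) }.

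Here |p₁ − p₂| = 0.1311, √(2p̄(1 − p̄)) = 0.4502 and the denominator is 0.4406.

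- n = 90: (0.1311 × 9.487 − 0.8824)/0.4406 = 0.820, so power is 0.794.
- n = 180: (0.1311 × 13.416 − 0.8824)/0.4406 = 1.990, so power is 0.977.

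Exact two-sided Fisher power was obtained by enumerating all outcomes.

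| n per arm | Corresponds to | Normal approximation | Exact Fisher |
|---|---|---|---|
| 90 | 200 in total, after attrition | 0.794 | 0.761 |
| 100 | 200 in total, before attrition | 0.835 | 0.801 |
| 180 | 200 per group, after attrition | 0.977 | 0.974 |
| 200 | 200 per group, before attrition | 0.986 | 0.986 |

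The normal approximation needs 92 per arm for 0.80 power. The stated 0.80 at 18% is reproduced with about 90 to 100 per arm and not with 180 or 200.

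**Step 5: the control rate that gives 0.80 power at OR 4.27.**

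| n per arm | Normal approximation | Exact Fisher |
|---|---|---|
| 90 | about 18.5% | about 20% |
| 100 | about 16.5% | about 18% |
| 180 | about 9.25% | about 10% |

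An 18% requirement belongs to the 200-total design. With 180 analysable per arm the requirement would have been about 9 to 10%.

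**Step 6: secondary outcomes.** The section states a detectable Cohen's f of 0.27 at 0.80 power. The article does not give the degrees of freedom, so this check rests on an assumption. For 1 to 5 numerator degrees of freedom, N = 180 detects f between 0.210 and 0.271, the upper end being 5 (2 groups × 3 times). N = 360 detects f between 0.148 and 0.190. The stated 0.27 can arise with 180 in total but not with 360 anywhere in that range.

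**The case against.** The strongest reply is that the article resolves the matter itself. The correct size appears explicitly twice, including in the section that governs randomization, and the attrition sentence agrees with it. Nothing else supports a 400-participant trial. On that view the phrase about each group is a slip, no analysis or power figure changes when it is corrected, and the factor of two describes a design nobody intends. The arithmetic in the section is also right once the total is taken as 200.

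Much of this stands. The error is one of wording, the intended size can be inferred with near certainty, and the trial's design is not in question. The ambiguity about when recruitment is complete arises only for a reader who takes the sample-size section at its word. But that section defines the target, and a reader should not have to reconstruct the power calculation to learn that its opening sentence is wrong.

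A second objection is that 200 in total does not reproduce the stated power exactly: with the planned Fisher test and 90 per arm, power is 76%. This is true. The stated 0.80 holds under the normal approximation at 90 per arm (0.794), or under Fisher at 100 per arm with no attrition (0.801). That is a separate matter of which method the power statement used. It does not affect the conclusion here, because 180 per arm misses the stated power by far more, at about 97%.

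**Conclusion.** The concern holds. The enrolment goal in the Sample size calculation section is twice the size given in the abstract and in Arms and interventions, and twice what its own attrition figure implies. Reading 180 as per group is excluded by the stated power: about 0.97 at 180 per arm, against 0.76 to 0.79 at 90 per arm, with 18% control progression and OR 4.27. The intended size is almost certainly 200 in total.

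The conclusion takes the article's own inputs (10% attrition, 18% control progression, OR 4.27, two-sided 0.05) and assumes equal attrition in the two arms when 180 is split into 90 and 90. The secondary-outcome check supports it but depends on assumed degrees of freedom. The consequence is a misstated core design parameter, not a flaw in the design.

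**What to change.** Reword the opening of the Sample size calculation section along these lines: *The enrollment goal is 200 participants in total, randomized 1:1 to intervention and control (100 per group). Allowing for 10% attrition, about 180 are expected to be analysable (about 90 per group).*

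Stating the per-group analysable number is not strictly needed to remove the contradiction, but it makes the basis of the power statement plain.

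The cost is a one-line correction. It brings the section into line with the abstract and Arms and interventions, and leaves the enrolment plan, effect size, 18% condition and secondary detectable effect as they are.

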#### Data analysis plan

We will use a modified intention-to-treat population approach and include participants with valid baseline data and at least one post-baseline data point. Missing data among these participants will be handled using multiple imputations, clearly described, and with sensitivity analysis to test the robustness of the results.

Primary outcome analysis will be completed using a Fisher’s exact test to compare the proportions of progression in the intervention and treatment groups. To analyze secondary and exploratory outcomes between groups, we will use mixed-effects regression models to evaluate change in outcome as a function of group, time, and group-by-time interaction. We will also conduct longitudinal analysis within groups using repeated measures ANOVA to compare measures at time points, with covariates as fixed effects. Effect sizes and confidence intervals will be reported. Additionally, we will assess baseline sample characteristics and test for any baseline group differences using two-sample t-tests for continuous variables and Chi-square tests for categorical variables. We will also conduct an adherence analysis by reporting intervention session attendance rate and summary statistics for self-reported engagement with intervention domains and testing for any differences in these adherence metrics based on cohort number, age/sex, and other covariates. We will conduct sensitivity analyses aligned with best practices to see if the outcome analysis results are robust to any potential confounders, including baseline imbalance or intervention non-compliance.

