### Perspective

This study will benefit from the enrollment of deeply characterized neurologically healthy older adults (≥ 50 years) with risk factors for the four most common neurological disorders that share clinicopathological features. We will test the impact of multidisciplinary lifestyle interventions (MLI; diet, yoga, music and cognitive training) delivered using videoconferencing technology, which has the potential to be highly accessible and scalable. We will analyze the impact of this MLI on a variety of patient reported outcomes. The study’s ability to detect a large effect of MLI on the primary outcome of clinicopathological progression with sufficient power via group analysis depends on an incidence of progression (> 18%), which may be difficult to attain in the limited 12-month study period. This limitation will be mitigated by analysis of possible dose effects across groups via the MLI engagement data and supported by analysis more sensitive secondary outcomes. Additionally, the multimodal, multi-omics tests (neurophysiology, neuroimaging, genomics, proteomics, metabolomics, gut microbiome transcriptomics) will help explore biomarkers of early disease progression and MLI’s impact on them. This study aims to contribute to the body of work aiming to develop effective early interventions for neurological disease in older adults as well as explore patient reported outcomes and biomarker candidates for use in future trials.

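### With Fisher's exact test on 90 per arm, power at 18% control progression is about 76%, not 80%; reaching 80% needs a control rate of about 20%

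*Protocol article*

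**What the plan says.** The statements come from four sections of the protocol article.

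- **Arms and interventions:** "Two hundred participants will be randomized equally to two study arms", that is, 100 per arm.
- **Sample size calculation, analysable number:** "Based on an attrition rate of 10%, we estimate we will have 180 participants with data for analysis".
- **Sample size calculation, effect and threshold:** the effect is a conventional large one ("odds ratio = 4.27, converted from" a Cohen's d of 0.8). Detecting it "at 0.8 power with a two-sided alpha of 0.05 would require 18% of the control group attaining progression". The section does not name the test behind this figure.
- **Data analysis plan:** "Primary outcome analysis will be completed using a Fisher’s exact test".
- **Perspective:** the ability to detect a large effect on the primary outcome "depends on an incidence of progression (> 18%), which may be difficult to attain" within 12 months.

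**The concern.** The 180 analysable participants come just before the 18%, so a reader takes the power statement to rest on 90 per arm. The only primary test named is Fisher's exact test, which is conservative with proportions this small. A threshold taken from a less conservative formula, or from the number before attrition, is then too low for the analysis that will be run.

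At stake is the accuracy of the one power statement for the primary outcome. The article already doubts that 18% can be reached, and the rate that the planned analysis needs is higher. The Perspective section also speaks of an incidence of progression without saying that it is the control-arm rate. Under the stated alternative the two arms together would show only about 11.4%, so anyone comparing pooled progression with 18% would use the wrong benchmark.

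**Working it through.** **Inputs**

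- Randomised: 200, 1:1 (Arms and interventions).
- Analysable: 200 × 0.9 = 180 (Sample size calculation), or 90 per arm if retention is equal (assumption).
- Odds ratio 4.27, power 0.80, two-sided alpha 0.05, control rate 18% (Sample size calculation).
- Test: Fisher's exact (Data analysis plan).
- The odds ratio is read as control odds over intervention odds, the direction of benefit (assumption).

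**Step 1. Effect size.** exp(0.8 × π / √3) = 4.268, so the conversion to 4.27 is right.

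**Step 2. Intervention rate.** Control odds = 0.18 / 0.82 = 0.2195. Divided by 4.27 this is 0.0514, and 0.0514 / 1.0514 = 0.0489, or 4.9%. The pooled rate is (18% + 4.89%) / 2 = 11.4%.

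**Step 3. Reproducing the plan's figure.** The normal approximation with pooled null variance and no continuity correction, at n = 90 per arm, is:

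power = Φ{ [ (p₁ − p₂) − 1.96 √(2 p̄ (1 − p̄) / n) ] / √( [p₁(1 − p₁) + p₂(1 − p₂)] / n ) }

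- Difference: 0.18 − 0.0489 = 0.1311.
- Null term: 1.96 × √(2 × 0.1144 × 0.8856 / 90) = 0.0930.
- Standard error under the alternative: √((0.1476 + 0.0465) / 90) = 0.0464.
- Result: Φ(0.0381 / 0.0464) = Φ(0.82) = 79.4%.

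The 80% point by this formula is a control rate of 18.3%. The stated pair of 18% and 80% therefore reproduces at 90 per arm, but with a test other than the planned one.

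**Step 4. The planned test.** Power was computed by enumerating every 2×2 table with fixed arm sizes, taking the two-sided Fisher p-value of each and adding the binomial probabilities of the tables with p ≤ 0.05.

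| Control rate | Intervention rate | Fisher, 90 per arm | Fisher, 100 per arm |
|---|---|---|---|
| 17% | 4.6% | 73.4% | 77.4% |
| 18% | 4.9% | **76.1%** | **80.1%** |
| 19% | 5.2% | 78.5% | 82.6% |
| 20% | 5.5% | 80.7% | 84.7% |

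Solving for 80% power gives a control rate of **19.7%** at 90 per arm and 17.96% at 100 per arm. With the control rate held at 18%, 99 per arm gives 79.6% and 100 per arm gives 80.1%, so 80% is reached only at about the number randomised.

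**Step 5. Could rounding or a convention explain the gap?** A control rate of 18.49%, which still rounds to 18%, gives 77.3%. Testing each tail at 0.025 gives the same 76.1%. Neither closes the gap.

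**The case against.** The strongest reply is that 18% is not a miscalculation. A standard two-proportion approximation at 90 per arm gives 79.4%, and the section does not say which test it used. What remains is the familiar gap between an approximate formula and a conservative exact test. It leaves type I error control, sample size and endpoint untouched. The effect size is itself a generic benchmark, and the Perspective section writes more than 18% and already presents it as a limitation. All of this stands and limits the weight of the point. It does not remove it, because the article fixes both the test and the analysable number, and together they do not give the stated power.

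The sample size section also writes "Our enrollment goal is 200 participants randomized to each group (intervention and control"). Read literally, with 10% attrition, this is 180 per arm, and Fisher power at 18% would be about 97%. That reading contradicts the 100 per arm stated elsewhere and, if 180 is the total, the section's own analysable number. It does not reproduce 80% at 18% either.

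Two stronger readings are tempting, and the documents support neither.

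- A reader might infer that 18% is a go/no-go criterion for the primary analysis. No interim look, stopping rule or re-estimation uses it; it appears as a power condition and as a limitation.
- A reader might infer that the secondary statement ("between group mixed-effects regression analysis, we will be able to detect a medium effect size", f = 0.27) is wrong too. Simple F-test calculations at N = 180 give smaller detectable effects (0.21 for 1 df, 0.23 for 2 df), so 0.27 errs on the cautious side. Detectable f in a mixed model depends on the within-person correlation and the contrast, which the article does not give, so it cannot be shown to be wrong.

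**Conclusion.** The stated threshold does not hold for the planned analysis. With Fisher's exact test and 90 analysable per arm, power at 18% control progression is 76.1%, so the chance of missing an odds ratio of 4.27 is about 24% rather than 20%. A control rate of 19.7% is needed for 80%. The shortfall is 3.9 points of power, or 1.7 points of control rate. The result assumes equal retention and an odds ratio in the direction of benefit.

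This is a modest correction to a stated figure, caused by a mismatch between the power statement and the planned test or analysable number. It does not threaten the validity of the primary analysis, and it leaves the article's own caution about reaching the required rate in place, with a slightly higher bar.

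**What to change.** In the sample size section, state that for Fisher's exact test with 90 analysable per arm, 80% power to detect an odds ratio of 4.27 requires about 20% progression in the control group (19.7%; power at 20% is 80.7%). Alternatively, keep 18% and state the power there as about 76%. In the Perspective section, use the same figure and call it the control-arm rate.

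The cost is wording in two places and a slightly less favourable threshold. Sample size, alpha, endpoint and primary test stay as they are. Changing the primary test to preserve 18% is not needed and would be more than a wording change, since the article says that enrolment began in July 2023.
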